### Hypotheses

In this study, we examined two hypotheses:

There is no difference in functional capacity between the HBECTR group and the control group (CG; H_0_) or HBECTR will improve functional capacity compared to the control (H_1_).There is no difference in adherence between the HBECTR group and the CG (H_0_) or HBECTR will improve adherence to CR compared to the control (H_1_).

## Methods

### Study Design

This trial is designed as a pilot feasibility study to evaluate the practicality, safety, and preliminary effects of HBECTR using a quasi-experimental nonequivalent CG pretest-posttest. Participants will be assigned to either the intervention group (IG), which will receive the HBECTR program, or the CG, which will receive standard care (CBCR). Pre- and post-intervention data will be collected to assess the impact of the HBECTR program on patients’ adherence as primary outcomes and their functional capacity as secondary outcomes.

We use a quasi-experimental design with a nonrandomized control group due to the limited number of eligible participants [26], the logistical and resource constraints, and to bringing the implementation closer to the real world. As a pilot study, we want to identify the feasibility of HBECTR in Indonesia. In fact, there is a strong need to further investigate and incorporate synchronous digital CR into the routine of cardiac patients’ secondary prevention routine [27].

### Settings

This study was being conducted since August 2024 and June 2025 at [name] General Hospital, Indonesia, focusing on patients after PCI. The intervention will be done in the CR center at [name] Hospital, Yogyakarta, and at the patients’ homes. The research environment will include outpatient clinics and remote monitoring settings where participants will receive either the HBECTR program or standard care. The setting will ensure access to medical records, availability of telehealth technologies, and close coordination with health care professionals to support the implementation and evaluation of the HBECTR program.

### Samples

The population consists of patients after PCI recruited using consecutive sampling. Sample size calculation was performed based on previous studies [15,28], with the minimum difference of 6-minute walk distance as 30 m [29,30]. We determined the patients based on the 95% CI, 80% power, 5% type I error, and 10% dropout rate. A minimum of 60 patients (30 per group) will be included, consistent with recommendations for pilot feasibility studies, which suggest 12‐30 participants per arm to estimate variability and assess feasibility parameters [31,32]. We will carefully select the samples based on the inclusion criteria: (1) patients with coronary artery disease after successful PCI, (2) aged 18 years or above, (3) covered by active health insurance (BPJS), (4) willing to participate and sign informed consent, (5) having internet connectivity at home (for the CG), (6) living with family or having a family member as a caregiver, and (7) able to read and understand Bahasa Indonesia.

Both groups will be recruited consecutively using identical eligibility criteria, recruitment procedures, and measurement protocols. This study uses a quasi-experimental nonequivalent control group design where the IG was recruited and completed follow-ups before the initiation of the control or comparison group. Sequential, nonconcurrent enrollment was selected due to practical constraints, including a limited number of eligible patients and complete essential preparatory activities and devices (smartwatch and dashboard setup, system testing, and staff training) prior to delivering the hybrid cardiac telerehabilitation intervention. Similar sequential recruitment approaches are common in pragmatic and feasibility trials where randomization or concurrent enrollment is not operationally feasible [26,33].

However, such nonconcurrent enrollment introduces potential time-related biases that statistical adjustment cannot fully eliminate [33]. To mitigate these concerns, we will implement two strategies. First, in the pre-intervention assessment, we will perform demographic and clinical assessments at baseline across both groups. We will carefully select patients based on the eligibility criteria, standardize all outcome measurements (attendance list, 6MWT) using the same instruments and trained team, and apply identical follow-up schedules. These data will help us statistically adjust for any identified differences, although we recognize that such adjustments may not completely eliminate bias. Second, in propensity score matching (PSM), we will plan to use PSM to equate the groups on key variables measured at baseline, which can help balance characteristics across the groups. Baseline demographic and clinical characteristics will be carefully documented, and differences between the groups will be statistically adjusted using multivariable regression and propensity score methods. The use of PSM enabled the construction of a comparison group comprising individuals similar to the treatment group individuals on most observable characteristics [34].

Blinding procedures are often not feasible in quasi-experimental studies due to the absence of randomized assignment and the practical realities of real-world intervention delivery, particularly in exercise, physical activity, and rehabilitation research [35]. In this study, the full blinding of participants and assessors was not possible because of the overt nature of the intervention and logistical constraints. Nevertheless, the risk of bias was mitigated by implementing several strategies: using validated measurement tools; providing objective and standardized outcome assessments; and, wherever feasible, ensuring that data analysts were blinded to group allocation during the data analysis phase. Data were coded such that the analysts were unaware of group assignments until after the completion of initial analysis (see Figure 1).

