### The Intervention Group

The patients in the treatment group will be prescribed an individually EBCR program at home and in the hospital. The targeted heart rate and walking distance targets will be set individually based on baseline 6MWT. The intensity progression will be evaluated weekly if tolerated. Exercise education and an exercise guidance book will be provided to patients before the program begins. In the hospital, patients do a 45-minute exercise session consisting of a warm-up (5 min), core exercise (30 min) in the form of walking on a treadmill, and cool down (10 min). This exercise is carried out twice a week over 4 weeks in the hospital (a total of 8 sessions) and is directly supervised by a certified cardiac rehab nurse (Table 1).

During exercise at home, subjects will be monitored by a “TEKAD” telemonitoring system. Patients will wear CovWatch that will be connected via the internet to a web-based system (App Rehab Cardio). Prior to the exercise at home, the researcher and the IT team will ensure that the CovWatch is connected to the dashboard App Rehab Cardio to facilitate the real-time monitoring of patients’ vital signs during exercise (see Figure 2). Home exercise will be carried out for 45 minutes, consisting of 5 minutes of warm-up (eg, simple stretching or slow walking), 30 minutes of core exercise walking based on the exercise dose and patient’s ability, and 10 minutes of cooling down. Vital signs, such as pulse, BP, and oxygen saturation, will be monitored via CovWatch and displayed on the dashboard. Home exercises will be prescribed 3 days a week over 4 weeks (12 sessions in total), with a schedule adjusted by the researchers so as not to coincide with the hospital exercise sessions. Patients will be evaluated and receive weekly exercise reminders directly when they perform exercise at the hospital.

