### The Control Group

The CG will be enrolled in a cardiac rehabilitation program in the hospital. Patients in this group also will receive exercise education before starting the program. They will be scheduled for 2 sessions per week or 8 sessions in total to do individual exercise at the hospital under a CR nurse’s supervision. Based on hospital policy, patients are also suggested to exercise at home independently (without monitoring). Hospital exercises consist of a 5-minute warm-up, 30-minute core exercise (walking on a treadmill), and a 10-minute cool-down (Table 1).

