### Measurement

In this study, respondents will be asked to fill out the participant characteristics, including age, sex, BMI, and medical history, which were collected at baseline through direct interviews and medical record reviews. Sociodemographic information, such as marital status, educational level, occupation, insurance ownership, and average monthly income, was also gathered. In addition, participants were asked about their smoking history (categorized as current, former, or never smoked) and any past or current illnesses, diseases, or risk factors. Clinical information was obtained, including the patient’s medical diagnosis, ejection fraction, prescribed therapies, weight and height, as well as the schedule of heart polyclinic control and cardiac rehabilitation, if applicable.

Adherence to the exercise-based cardiac rehabilitation program as the primary outcome will be measured by recording the number of sessions attended by each participant. Based on a previous study [40], adherence will be calculated as the number of attended sessions divided by the total number of prescribed sessions, expressed as a percentage, with a minimum of 80% session completion considered adherent. Attendance during in-hospital exercise sessions will be directly monitored by CR nurses and recorded in the CR attendance form, while home-based exercise attendance for IG will be verified through the web-based dashboard system. Adherence will be monitored by smartwatch logs and dashboard analytics. We will apply this comprehensive approach to ensure accurate measurement of each participant’s adherence to the prescribed rehabilitation program.

Functional capacity will be assessed using the 6MWT to measure the total distance (in meters) during 6 minutes test (6-minute walk distance) [19,37]. In addition, physiological data such as HR, BP, and oxygen saturation will be continuously monitored using the telemonitoring system (see Figure 2), ensuring the safety and accuracy of HBECTR. To provide a more comprehensive assessment of functional improvement, peak oxygen uptake (VO_₂_ peak) or metabolic equivalents will be estimated based on the distance covered in the 6MWT, using established predictive equations [41,42]. These measurements collectively will provide robust data on the participants’ functional performance following the intervention.

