To analyze the effects of HBECTR on patient adherence as the primary outcome and functional capacity as the secondary outcome, there is no formal multiplicity adjustment planned. The data analysis based on normality assumption will be tested using the Shapiro-Wilk test. If the data comply with the normal assumption, we will use the Student *t* test, and vice versa, nonparametric tests will be used if assumptions are violated. In all statistical tests, *P*<.05 (95% CI) will be considered statistically significant. This structured approach will ensure that statistical methods are properly tailored to the data, supporting robust and meaningful interpretation of the results. The statistical analysis plan has been registered within the protocol to the institutional ethics committee board with the approval number KE/FK/0850/EC/2024.

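### For percentage adherence, the primary outcome, a group code alone cannot keep the analysts unaware of group, because control moves in eighths and intervention in twentieths

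*Protocol article*

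**What the plan says.** The blinding paragraph in the Samples section concedes that participants and assessors could not be fully blinded. It then lists measures said to reduce the risk of bias: validated tools, objective and standardised assessment, and "wherever feasible, ensuring that data analysts were blinded to group allocation during the data analysis phase". The next sentence drops the qualifier: "Data were coded such that the analysts were unaware of group assignments until after the completion of initial analysis".

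The Measurement section defines the primary outcome: "adherence will be calculated as the number of attended sessions divided by the total number of prescribed sessions, expressed as a percentage". It also sets a threshold that turns this into a yes/no variable: "with a minimum of 80% session completion considered adherent". The number of prescribed sessions differs by group:

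- Control: "They will be scheduled for 2 sessions per week or 8 sessions in total to do individual exercise at the hospital".
- Intervention, at the hospital: "This exercise is carried out twice a week over 4 weeks in the hospital (a total of 8 sessions".
- Intervention, at home: "Home exercises will be prescribed 3 days a week over 4 weeks (12 sessions in total".

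The Statistical Analysis Planning section proposes paired t tests or analysis of covariance, with means and SDs, for functional capacity and for adherence. It checks normality with the Shapiro-Wilk test, uses the Student t test if normality holds, and otherwise "nonparametric tests will be used if assumptions are violated". Patients with both assessments stay in the outcome analysis whatever their adherence level.

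**The concern.** Masking of the analysts is the only blinding the article claims. It matters because several analysis choices are left open until data are in hand: t test or analysis of covariance, propensity matching with multivariable regression (Samples) or exploratory propensity adjustment (Statistical Analysis Planning), and covariates named only as examples. If the primary outcome itself shows which coded group is which, those choices can be made with the group known. A report that repeats the blinding sentence would then credit the primary analysis with a protection it did not have.

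**Working it through.** **Inputs.** Prescribed sessions come from the two group descriptions and agree with Table 1:

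- Control: 2 per week × 4 weeks = 8.
- Intervention: 2 × 4 = 8 at the hospital plus 3 × 4 = 12 at home, total 20.

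The group size of 30 comes from the Samples section. The article gives no attendance rate, so per-session attendance is an assumption, varied from 0.50 to 0.995.

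**Possible values.** Control adherence is k/8 with k = 0 to 8, which gives 9 values. Intervention adherence is j/20 with j = 0 to 20, which gives 21 values. A value can occur in both groups only if k/8 = j/20, that is 5k = 2j, so k must be even: k = 0, 2, 4, 6, 8.

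- Shared: 0, 25, 50, 75 and 100% (5 values).
- Control only: 12.5, 37.5, 62.5 and 87.5% (9 − 5 = 4 values).
- Intervention only: 21 − 5 = 16 values.

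One missed session gives 7/8 = 87.5% in control and 19/20 = 95% in intervention. Neither value is possible in the other group.

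**Single patients.** Let q_C and q_I be the binomial probabilities that a patient's percentage is one of the five shared values, with 8 and 20 trials respectively. At attendance 0.80, q_C = 0.51 and q_I = 0.19. At 0.95 they are 0.72 and 0.36. A single record is therefore often uninformative.

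**Coded groups.** With two coded groups, one telltale value anywhere identifies both. The chance that none appears among 30 + 30 patients is q_C^30 × q_I^30:

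| Assumed per-session attendance | Chance that no telltale value appears |
|---|---|
| 0.50 to 0.95 | below 1e-17 |
| 0.98 | 6e-8 |
| 0.99 | 0.0002 |
| 0.995 | 0.015 |

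Attendance is likely to be uneven across patients, so a mixture was also tried: a fraction of patients completes every session and the rest attend each session with probability 0.70. The chance is 0.0002 if 80% complete everything, 0.018 if 90% do, and 0.14 if 95% do. Concealment becomes plausible only when almost every patient has perfect attendance.

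**The yes/no version.** At the 80% threshold, control needs at least 0.8 × 8 = 6.4, hence 7 of 8, and intervention needs 0.8 × 20 = 16 of 20. As a 0/1 variable both groups hold the same two values and the signature disappears. But a Shapiro-Wilk test, a t test and means with SDs need the percentage.

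**Other cues.** The Samples section says the intervention group completed follow-up before the control group started, so any date separates the groups. Home attendance is verified on the dashboard for the intervention group only (Measurement), and home exercise in control is unmonitored (The Control Group). Each cue works only if the field is in the analysts' file, and the article does not describe that file.

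**The case against.** A reader might infer that analyst blinding is impossible anywhere in this trial and that dates, dashboard data and adherence all give the group away. The documents do not support that:

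- The claim is qualified once by feasibility and covers only the initial analysis.
- Dates and dashboard fields can be removed. What the file contained is data-management detail that an article may leave to the full protocol.
- Walk distance has the same scale in both groups, and so does the yes/no form of adherence.
- Values such as 100% fit either group, so not every patient is identified.

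All of this stands, and it confines the point to percentage adherence.

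It can also be said that the choice between t test and nonparametric test follows a stated normality rule that does not depend on knowing the group, and that propensity adjustment is labelled exploratory. That weakens the likely consequence. It does not cover the choice between t test and analysis of covariance, or the open covariate list.

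The drop-out criteria, read literally, would remove anyone who did not complete the full programme, leaving only 100% values. The analysis section says otherwise, since it keeps completers of both assessments whatever their adherence.

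Finally, the count of telltale values shows that the group can be recognised. It does not show bias in any estimate, and the article is open about limited blinding and about time-related bias that adjustment cannot fully remove.

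**Conclusion.** The point holds for percentage adherence. There, the unqualified sentence on coding conflicts with the article's own outcome definition and session counts: a group code alone would almost certainly be broken by the data.

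This rests on three assumptions: every patient is prescribed 8 or 20 sessions as described, the analysts receive adherence as a percentage, and the initial analysis includes it. The planned tests make the second likely. The article settles neither the second nor the third explicitly.

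It does not follow that the walk-distance analysis was unmasked, or that any analyst acted on knowledge of the group. Severity is minor. The larger risks of bias are open treatment, unblinded assessors and sequential, non-randomised enrolment.

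**What to change.** 1. In the blinding paragraph, and in the results report, state that the analysis of percentage adherence is not masked. Limit the blinding claim to outcomes for which masking is possible.
2. For 6-minute walk distance, give the analysts a file with only the arm code, baseline covariates and distances. Leave out dates, session counts and all dashboard or home-exercise variables.
3. Fix and date the propensity model, the covariates and the choice of test on an outcome-free file before outcomes are linked. The Results section says analysis was already under way, so where this is no longer possible, report which choices were made after the group could have been known.

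The cost is a revised paragraph, one extra data cut and a less favourable statement of the safeguard for the primary outcome. Step 3 may be only partly achievable at this stage, and the disclosure then takes its place.

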**Figure 1. F1:**
[figure not shown]
CONSORT (Consolidated Standards of Reporting Trials) flow diagram.

### Study Procedures

To assess the efficacy of the HBECTR program, we divided subjects into 2 groups: the intervention group and the control group (Table 1). The CG will receive standard hospital CR or CBCR, while the treatment group will receive HBECTR. We define HBECTR as exercise-based cardiac rehabilitation conducted in a hybrid setting, both in the hospital and at the patient’s home, supported by a telemonitoring system.

We will use a telemonitoring system consisting of a smartwatch (CovWatch) produced by PT CovWatch Karya Nusantara, Indonesia, connected via the internet to the web-based app (dashboard), namely “Telerehabilitasi Kardiovaskular (TEKAD)” (App Rehab Cardio) [36]. We developed and conducted usability testing before the dashboard was released (will be reported separately). Prior to the initiation of the study, an accuracy test will be conducted on 10‐20 patients as part of the CovWatch protocol. A standardized calibration check will be performed at baseline by comparing CovWatch-derived heart rate (HR) with a clinical pulse oximeter at rest and during walking test. Data validity will be monitored through automated system flags for missing data, connectivity loss, and out-of-range physiological values. Mitigation strategies will include repeating measurements, instructing participants on proper device placement (detailed in the guidance book for patient), verifying battery status, and resynchronizing data in case of delayed transmission. All sensor data will be stored with time stamps to identify anomalies and enable manual quality checks.

Before starting the exercise, all patients will undergo a pretest to measure functional capacity using the 6-minute walk test (6MWT) [37]. This pretest is carried out when the patient is still hospitalized or during the first check-up after PCI, according to hospital policy. The cardiologist will prescribe an exercise regime tailored by patients based on this baseline 6MWT, in accordance with the CR guidelines in Indonesia [19]. After the patients have finished all CR programs, they will do the 6MWT for a posttest. The 6MWT for both pretest and posttest will be done at the CR center, [name] Hospital, Yogyakarta. The intervention of this study will be reported according to the TIDieR (Template for Intervention Description and Replication) [38], in conjunction with the CERT (Consensus on Exercise Reporting Template) [39] and mERA (mHealth Evidence Reporting and Assessment; Checklist1^4^).

**Table 1. T1:** Exercise prescription based on frequency, intensity, time, and type (frequency, intensity, time, and type) for the control group and the intervention group.

Dose	CG^a^ (CBCR^b^)	IG^c^ (HBECTR^d^)
Frequency	Standard care included 2 sessions per week at the hospital	5 sessions per week, divided into 2 sessions per week at the hospital and 3 sessions per week at home
Intensity	Moderate	Moderate
Time	45 min Warm-up: 5 min Core-exercise: 30 min Cool-down: 10 min	45 min Warm-up: 5 min Core-exercise: 30 min Cool-down: 10 min
Type	Aerobic (ergo cycle and treadmill)	Aerobic: ergo cycle and treadmill at the hospital; or walking on flat ground at home
Monitoring	Hospital: supervised by CR^e^ nurse based on vital signs, distance, RPE^f^, and %HRR^g^	Hospital: supervised by CR nurse based on HR^h^, BP^i^, SaO_2_^j^, distance, RPE, and %HRR Home: monitored by smartwatch connected to dashboard (App Rehab Cardio), based on HR, BP, SaO_2_, distance, and patients' complaints

a CG: control group.

b CBCR: center-based cardiac rehabilitation.

c IG: intervention group.

d HBECTR: home-based exercise cardiac telerehabilitation.

e CR: cardiac rehabilitation.

f RPE: rate of perceived exertion

g HRR: heart rate reserve.

h HR: heart rate.

i BP: blood pressure.

j SaO_2_: oxygen saturation.

